## Abstract

**Background:**

Virtual reality (VR) is an innovative tool that can facilitate exposure to either stressful or relaxing stimuli and enables individuals who have difficulties visualizing scenes to be involved in a more realistic sensorimotor experience. It also facilitates multisensory stimulation, a sense of presence, and achievement of relaxation. VR scenarios representing visual and auditory elements of natural relaxing environments can facilitate the learning of relaxation techniques such as the progressive muscle relaxation technique (PMRT). A complementary standardized technique deployed to reduce anxiety symptoms is the integration of PMRT and guided imagery (GI). Exposure to a pleasant imaginary environment helps the establishment of an association between a relaxing scenario and the relaxation technique, consequently promoting relaxation. Empirical evidence has shown that VR scenarios can increase the effects of relaxation techniques by enabling people to experience emotional conditions in more vivid settings.

**Objective:**

The main aim of this pilot study protocol is to investigate the impact on state anxiety of PMRT, associated with a personalized relaxing scenario in VR, and the role of VR scenarios in facilitating the recall of relaxing images and a sense of presence. A secondary aim is to understand if relaxing sessions administered via Zoom are more effective for managing anxiety and stress than a procedural setting based on audio-track guidance.

**Methods:**

Based on a longitudinal, between-subject design, 108 university students will be randomly exposed to one of three experimental conditions: (1) PMRT via Zoom and GI exposure, (2) PMRT via Zoom and personalized VR exposure, and (3) PMRT based on audio-track guidance and personalized VR exposure. Individuals are assessed before and after 7 training sessions based on self-report questionnaires investigating anxiety, depression, quality of life, coping strategies, sense of presence, engagement, and side effects related to VR exposure. Heart rate data are also detected by an Mi Band 2 sensor.

**Results:**

The experimental procedure is ongoing. In this paper, preliminary data from a sample of 40 participants will be illustrated. The experimental phase is expected to conclude in May 2023, and the final results of the research will be presented in June 2023.

**Conclusions:**

The results of this study will help shape the experimental design to apply it on a subsequent randomized controlled trial, also considering clinical samples. This work is expected to measure whether VR is a more engaging and helpful technique in promoting relaxation and decreasing anxiety levels than GI, by making the visualization process easier and by helping people to face more realistic sensory experiences. Assessing the efficacy of the PMRT in alternative delivery modes may extend its applications, especially in situations where the standard procedure is more challenging to be administered. To our knowledge, no equivalent study has been published so far on this matter.

**Trial Registration:**

ClinicalTrials.gov NCT05478941; https://clinicaltrials.gov/ct2/show/NCT05478941

**International Registered Report Identifier (IRRID):**

DERR1-10.2196/44183

## Introduction

### Background

Virtual reality (VR) is widely used to treat various mental diseases [1], also in association with different types of relaxation training (eg, progressive muscle relaxation training), and it facilitates multisensory stimulation, sense of presence, and achievement of relaxation [2,3]. VR can facilitate the learning of relaxation techniques through exposure to scenarios in which natural environments, which are commonly considered relaxing, are shown [2]. VR also has several advantages such as follows: easy to use, user-friendly, promotes engagement, and allows a full multisensory immersion in the virtual experience facilitating the control of external disturbing stimuli [4,5].

It was also highlighted that the customization of VR environments is an element that promotes relaxation. This latter type of user-centered approach [6] allows individuals to experience more realistic emotional conditions, like those experienced in everyday life, and it enhances relaxation, sense of presence, and perception of security in the virtual context (eg, [7]).

Standard relaxation programs usually include more directive techniques that imply larger involvement of the cognitive functioning system (eg, hypnosis) or the physiological response system (eg, progressive muscle relaxation technique [PMRT]), as well as fewer directive procedures that may be based on the cognitive functioning control (eg, meditation) or the physiological feedback (eg, autogenic training), respectively [8]. All these protocols are effective in promoting relaxation.

Jacobson [9] developed the PMRT protocol in 1938, suggesting that the overactivation of the sympathetic nervous system is primarily responsible for excessive skeletal muscle activity. Thus, interference in the skeletal muscle activity based on progressive relaxation reduces the activation. This process also positively affects other physiological parameters (eg, heart rate frequency) [10,11].

On these grounds, the training consists in learning how to tense and release several muscle groups.

Evidence suggests that stress-competing relaxation techniques are among the most effective training programs for enhancing psychological resources and reducing psychological distress [12].

PMRT is based on “top-down” and “bottom-up” neuronal processing. The “top-down” pathway is turned on by higher cognitive activities, such as focused attention, related to the cerebral cortex and the cerebellum, which send commands to peripheral areas by controlling muscle tension and gradual release. The holding and releasing activities allow proprioceptive stimulation from peripheral sensory afferents to the higher nervous system regions via the spinal cord and the brainstem as a “bottom-up” pathway [13-15]. Also, based on these processes, PMRT is considered one of the most effective and adaptable techniques for relaxation, anxiety management, stress, and depression reduction considering different kinds of target populations (eg, nonclinical individuals, patients with cancer, chronic pain, osteoarthritis, heart disease, chronic headache, anxiety, and depression) [16-20].

Still, the administration of combined methods appears very useful in reducing anxiety and the perception of pain in patients with medical conditions or during pregnancy [19-21]. Indeed, complementary methods that imply the administration of integrated cognitive and behavioral procedures are studied to manage anxiety, stress, depression, and pain, particularly in populations such as patients with cancer. Notably, the integration of PMRT and guided imagery (GI) enhances and facilitates the effect of relaxation, reducing anxiety and depression symptoms [19,22].

The application of GI, or VR, and PMRT is based on classical conditioning theory that involves learning relaxation techniques and exposure to relaxing mental images as conditioned stimuli useful for overcoming stress and specific fear [23,24].

The integration of PMRT and GI has been highlighted in the literature as an effective complementary method for reducing pain and anxiety symptoms (eg, [19,21]). GI is useful in creating mental imagery and refocusing attention on positive and relaxing imagined visual, auditory, tactile, or olfactory sensations, resulting in specific psychological and physiological responses, such as relaxation [25]. GI may also increase the reduction of the autonomic nervous system responses [19,25,26]. This combination can promote a higher sense of relaxation during training sessions, but it should also play a role in recalling a state of relaxation during everyday activities.

The combined methods introduced by Baird and Sands [19] implement eight steps [27-31]:

Setting a comfortable and protected real environment in which to relaxRecreating an imagined scene involving different sensesGuiding the user in focusing on breathingUsing passive progressive relaxation techniquesRecalling the imagined scene to direct the attention to pleasant stimuliFeeling a release from pain and activation (eg, imagining a decrease in painful sensations)Imagining moving into the scene by continuing to use focused breathing and relaxationEnding the session (“Breathe deeply. When you are ready, allow the image to fade. Stretch and open your eyes” [19]).

Considering the positive impact on relaxation of GI associated with PMRT, exposure to a more vivid, closer-to-reality virtual experience should be a useful technique in further improving the relaxation learning promoted by the PMRT.

Furthermore, it is well known that before delivering PMRT with GI, some sessions of PMRTs, focused on learning to recognize and relax the muscle areas of our body, are needed. Usually, these training sessions are administered face-to-face in the therapist’s presence. Finally, to investigate the effectiveness of web-based psychotherapy interventions, there are controversial results regarding a PMRT procedure administered in vivo or via audio-tracks [32-34]. To our knowledge, no recent study exists addressing the comparison among training sessions administered in vivo, in a remote modality, or via audio-tracks. In light of the pandemic due to SARS-CoV-2, we intend to explore PMRT’s efficacy in a remote situation via both Zoom and audio-tracks.

In general, it is essential to point out that remote treatments have been increased. They promote users’ independence in managing some psychotherapy techniques, leaving time for other face-to-face psychotherapy activities that require the active involvement of both the patient and the therapist. Assessing the efficacy of PMRT in alternative settings may facilitate the administration of treatment where it is impossible to implement the standard procedure. It may also increase the positive impact of abbreviated relaxation session and combining relaxation methods with patients who have chronic pain or must be exposed to invasive medical treatments (eg, chemotherapy) [35,36].

### Study Overview and Objectives

The purposes of the present research project are as follows:

Investigating if PMRT associated with a personalized relaxing scenario in VR can facilitate relaxation and lower state anxietyUnderstanding if the VR scenario helps recall the relaxing image assessed during the follow-up sessionInvestigating if VR is more effective in promoting the association between the relaxing scenario and PMRT than the standard procedure, consisting of PMRT associated with the imagery-induced exposure to a subjective relaxing environmentAnalyzing if the relaxing sessions administered via Zoom are more effective in managing anxiety and stress than a procedure administered via audio-tracks.

We hypothesize that VR would be more effective than GI in promoting relaxation and decreasing state anxiety because it would facilitate the visualization process, allowing individuals to have more realistic sensory experiences than imagery-induced exposure.

## Methods

### Ethics Approval

This study protocol involving human participants was General Data Protection Regulation compliant and developed following the Declaration of Helsinki (Italian law 196/2003, European Union General Data Protection Regulation 679/2016). The institutional review board of the Interdepartmental Ethical Committee of Psychology (17 Area) of the University of Padova (Italy) approved the study protocol on May 28, 2021 (approval number 4213). In February 2022, the trial was tested based on a convenience sample of 5 individual volunteers from the general population. Then, it was decided to introduce the following questionnaires: the Coping Orientation to the Problems Experienced-New Italian Version (COPE-NVI), the ITC-Sense of Presence Inventory (ITC-SOPI), the Vividness of Visual Imagery Questionnaire [37,38], and the Test of Visual Imagery Control [37,38]. The amendments and supplementations have been accepted, and the protocol received the final approval of the institutional review board of the Interdepartmental Ethical Committee of Psychology (17 Area) of the University of Padova, Italy (approval number 4701; April 29, 2022). Before their study enrollment, the participants signed a written informed consent form based on a paper-and-pencil form, agreeing to participate in all the study sessions.

They were informed that (1) their data would be confidential, (2) they could omit any information they did not wish to give, and (3) they could withdraw from the study without providing any explanation.

### Eligibility, Recruitment of Study Participants, and Randomization

The recruitment phase started in May 2022. Study participants were recruited in Northeast Italy via social networking websites (eg, Facebook groups) and by providing information on the research during university lectures. Those interested in participating were asked to make an appointment with the investigators to participate in the first assessment phase (T0) in which the inclusion and exclusion criteria were evaluated, written informed consent was obtained, and a baseline evaluation was made.

Eligible participants were adults from the general population (18 years or older), native Italian speakers, owning a PC, and able to use a PC and smartphone.

Participants were excluded from the study if they had been diagnosed with a severe mental disorder or medical conditions that could hinder their participation in the study (eg, neuromuscular disorders, severe psychiatric or neurological disorders, and assumption of drugs that could interfere with heart rate assessment and the subjective relaxation state), or if a psychotherapeutic treatment was ongoing.

Eligible participants were randomly allocated to 1 of 3 experimental conditions based on a simple blinded randomization via an Excel (Microsoft Inc) file.

Two experimenters, trained in cognitive and behavioral psychotherapy, conducted the relaxation sessions, each administering to 50% of the sample of each group to control for possible biases related to the therapist’s personality and competence. The 2 therapists who administered the experimental procedure received the same PMRT training and were supervised by a senior researcher and psychotherapist supervisors.

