### Power Calculation

Sample size estimation was computed with G*Power 3.1 software (Heinrich Heine Universität Düsseldorf) [43]. As a statistical test, the repeated-measures ANOVAs between factors have been considered. The effect size was set as 0.25, the α as .05, and the Power (1β error probability) as 0.80. We have 3 separate groups and 3 measurements. On the basis of these parameters, we estimated having to recruit at least 36 participants for each of the 3 groups.

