## Results

As of July 2022, a total of 45 individuals have been assessed as eligible for study enrollment (Multimedia Appendix 2).

Preliminary data showed adequate Cronbach α for all the T0 self-report questionnaire scores (ranging from .66 to .83). No differences emerged between the GI and VR groups at the baseline (T0) for all the sociodemographics and psychological features investigated (gender, marital status, school attendance, employment, participation in relaxation training in the past, use of VR in the past, anxiety, depressive and stress symptomatology, and the ability to imagine in a vividness way mental images) except for age (*F*_1,39_=12.32; *P*<.001) and years of education (*F*_1,39_=4.81; *P*=.04), factors that have been controlled for in the following group comparisons. To preliminarily investigate the differences between the VR and GI groups in experiencing state anxiety before and after the relaxation session (T1) and at T2, repeated-measures multivariate ANOVAs have been computed. At T1, our preliminary analysis showed a significant difference of the state-anxiety symptoms (*F*_1,39_=22.48*;*
*P*<.001) between groups with lower scores in state anxiety (VR group: mean 30.10, SD 4.35; GI group: mean 39.35, SD 4.71; *t*_1,39_=5.92*;*
*P*<.001) for the VR group after the relaxation session. Moreover, the VR group perceived a higher sense of physical presence (*F*_1,39_=7.38*;*
*P*<.01). The study’s experimental phase is expected to conclude in May 2023, and the results of the research will be presented in June 2023. The results obtained from this work will be published in an open-access scientific paper and in the form of posters and conference papers to be presented at national and international conferences.

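### Simple randomisation is very unlikely to give the planned 36 per arm from 108; the model omits the balanced therapist factor, and the preliminary covariates were picked by baseline significance.

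*Protocol article*

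**What the plan says.** The section on eligibility, recruitment and randomisation states: "Eligible participants were randomly allocated to 1 of 3 experimental conditions based on a simple blinded randomization via an Excel (Microsoft Inc) file". It mentions no blocking, stratification or ratio. The abstract's Methods give the total: "108 university students will be randomly exposed to one of three experimental conditions". The Power Calculation section gives the arm size: "we estimated having to recruit at least 36 participants for each of the 3 groups".

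The randomisation section adds that two experimenters ran the relaxation sessions, "each administering to 50% of the sample of each group". The stated purpose is to control bias from the therapist's personality and competence. How participants were assigned to a therapist is not described.

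The section on statistical procedure describes a mixed-design repeated-measures ANOVA with individuals as the random effect and intervention type and time as the fixed effects. Therapist is not named, and no covariates are listed.

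The Results section compares the GI and VR groups at T0 on a list of characteristics. It finds differences in age (F(1,39) = 12.32, printed P<.001) and years of education (F(1,39) = 4.81, printed P=.04), and calls these "factors that have been controlled for in the following group comparisons".

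**The concern.** Three statements in the article do not fit together well.

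- **Allocation and arm size.** A fixed total of 108 with at least 36 per arm leaves no slack. Simple randomisation lets arm sizes vary, so the stated method does not support the stated target.
- **Therapist.** The design treats therapist as a source of bias worth balancing, but the model has no term for it. If therapists differ, that variation stays in the between-subject error and the arm comparison becomes less precise.
- **Covariates.** Adjusting for whatever reached significance at baseline lets chance choose the adjustment set. Outcome results have already been reported (state anxiety at T1, F = 22.48). A covariate set still open at this stage could therefore be settled, or be seen to be settled, with the VR effect in view.

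**Working it through.** **1. The plan's own sample size.** Inputs from the Power Calculation section: "The effect size was set as 0.25, the α as .05, and the Power (1β error probability) as 0.80", and "We have 3 separate groups and 3 measurements". The correlation among repeated measures (ρ) is not given, so 0.5 is assumed. For the between-factors test:

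- λ = f² × N × m / (1 + (m − 1)ρ) = 0.0625 × 108 × 3 / (1 + 2 × 0.5) = 10.125
- df = 2 and 105; power = 0.809

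The smallest multiple of 3 with power of at least 0.80 is N = 108, or 36 per arm, so the stated figure is reproduced at ρ = 0.5. At other values of ρ the required N is 57 (ρ = 0), 87 (0.3), 129 (0.7) and 138 (0.8).

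**2. Arm sizes under simple randomisation of 108.** Exact multinomial with probability 1/3 per arm:

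- P(36/36/36) = 108! / (36!³ × 3¹⁰⁸) = 0.0076, about 1 in 131
- P(at least one arm below 36) = 1 − 0.0076 = 0.992
- Expected smallest arm = 31.0; P(smallest arm ≤ 30) = 0.38
- 95% range for any one arm: 27 to 46
- Total N for every arm to reach 36: about 131 (80% assurance), 137 (90%) or 142 (95%)

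**3. What that costs in power (ρ = 0.5).** With unequal arms, λ = Σ nᵢ(μᵢ − μ̄)² × m / (1 + (m − 1)ρ), where μ̄ is the weighted mean and f = 0.25 at equal sizes.

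| Allocation | Power |
|---|---|
| 36/36/36 | 0.809 |
| Average over simple randomisation | 0.803 |
| 28/40/40, small arm at one end of equally spaced means | 0.776 |
| 28/40/40, small arm the only one that differs | 0.745 |

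The average loss is about 0.6 percentage points.

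**4. Would equal blocks from now on repair it?** Suppose all 45 people reported as eligible were already allocated by simple randomisation, leaving 108 − 45 = 63. Equal blocks then add 21 per arm and carry the earlier imbalance forward. The target is met only if the first 45 split 15/15/15: 45! / (15!³ × 3⁴⁵) = 0.018. The expected smallest arm is 32.8. Equal blocking is therefore not enough; the remaining list has to hold the places each arm still lacks.

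**5. Printed P values at baseline.** F(1,39) = 12.32 gives p = 0.00115, and with 38 denominator df (40 people, two groups, no covariates) p = 0.00117. Neither is below .001. For education, F(1,39) = 4.81 gives p = 0.034, printed as .04.

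**The case against.** The strongest reply is that this is a condensed article about a proof-of-concept study. An Excel file can hold a shuffled list with 36 per arm, and the target reads as a minimum, so recruiting past 108 would meet it. The average power loss is under one point. The covariate adjustment belongs to a preliminary look at 40 people, and the final covariates and a therapist term may be in an analysis plan that is not shown. Intervention B's first four sessions are self-managed, so therapist contact there is limited.

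Much of this stands. The split is improbable, not impossible, and the power harm is small. Nothing in the article says that the final covariates will be chosen by baseline tests. What remains is that the stated method and the stated target do not fit. If a restricted list was used, the word simple is wrong. The article does name the model's fixed effects, and therapist is not one of them.

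A reader might infer three stronger things that the document does not support:

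- **That simple randomisation rules out the 50% therapist split.** Assigning therapists is a separate step. It can be alternated or blocked within arm whatever the arm sizes, to within one person.
- **That the age difference shows allocation was predictable or not followed.** Valid randomisation produces a p this small at its nominal rate. The comparison is GI against VR, not the three arms; it is one of about ten baseline tests; and the article does not say how the 40 analysed relate to the 45 eligible. Blocking on arm size would not have balanced age either.
- **That the standard errors are wrong.** Leaving out a balanced factor usually makes them too wide. No therapist effect is reported, so no size can be given.

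**Conclusion.** The point holds as a fit-and-specification problem, not as evidence of failed randomisation. Under simple randomisation as worded, 108 participants give 36 per arm about once in 131 trials, with an expected smallest arm of 31. The average effect on power is minor (0.809 to 0.803), though an unfavourable 28/40/40 split brings it to 0.745 to 0.776. The power figures rest on an assumed ρ of 0.5; the arm-size probabilities need only equal, independent allocation.

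Omitting therapist costs precision only if therapists differ, by an amount the document does not allow one to estimate. Choosing covariates by baseline significance is documented for the preliminary analysis only, and the recommendation is not to carry it forward. The printed P<.001 for age is a separate small error, because the printed F gives p = 0.0011.

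**What to change.** **Allocation.** For participants not yet randomised, use a concealed, randomly permuted list holding the places each arm still needs to reach 36, arranged within therapist. If a restricted list was in fact used, replace the word simple and name the restriction. If allocation is already complete, restate the expected arm sizes.

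**Model.** Add therapist as a fixed effect. Fix age and years of education as covariates now, whatever their significance. Handle T0 STAI-Y1 in one stated way: as a covariate if T1 and T2 are the outcomes, or as the T0 level of the repeated measure, but not both. Stop using baseline significance tests to choose covariates.

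**Reporting.** Correct the P value for age, and check the denominator df of 39 against 40 people in two groups.

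**Cost.** An amendment to change the allocation list part-way, plus a sensitivity analysis with a term for allocation before or after the change. The model changes take a sentence or two and remain possible after recruitment closes.

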Four sessions of active progressive muscle relaxation, in which participants are required perceptively learn the differences between the tension and relaxation of different muscle sections of the body. Each session has a duration of approximately 25 minutes. The first session is dedicated to the hands, forearms, arms, neck, shoulders, and back; the second to the facial muscles; the third to the diaphragmatic breathing; and the fourth to the abdomen, buttocks, and lower limbs. These sessions take place via the Zoom platform and are conducted by a cognitive-behavioral psychotherapist. Each Zoom session consisted of filling out 2 measures for the state anxiety and relaxation state based on the Moodle e-learning platform, sharing general standardized instructions for conducting relaxation and the rationale of the PMRT, guided relaxation aimed at relaxation of a dedicated body site, and filling out the same measures administered at the beginning of the session. A profile was created for each participant to access the Moodle platform. For the participants in condition “intervention B” (described in the following section) who participated in the first 4 PMRT sessions through the audio-track, all sessions were self-managed within the Moodle platform. Various activities have been scheduled based on the beginning of the training and the end of the activities planned in previous sessions.The fifth VR session is administered at the University of Padova Laboratory. All participants are asked to wear a smartwatch for heart rate detection. A total of 5 measurements (1 per minute) are made before the VR experience, 12 during the entire exposure in the virtual environment, and 5 after the experience in the virtual context. A duration of approximately 12 minutes has been established to avoid potential cybersickness symptoms during the virtual experience. This brief relaxation session is practiced by inexperienced individuals allowing for a decrease in anxiety and negative mood [40,41].

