### Statistical Procedure and Data Analysis

Quantitative statistical analyses will be performed using SPSS (versions 27.0 and 28.0; IBM Corp) [60,61] and R package [62]. To investigate the normal data distributions of the dependent variables, ranges of skewness and kurtosis will be determined. The Kolmogorov-Smirnov and the Shapiro-Wilk tests will also be performed to evaluate the statistical significance (mean, 95% CI) and normality of the distributions. In addition, Cronbach α will be assessed for each self-report questionnaire’s subscales. To explore sociodemographic features, frequencies, means, and SDs will be measured.

To examine differences between and within subjects, the 3 groups will be evaluated by a repeated-measures ANOVA for mixed designs, where individuals will be the random effect, while the type of intervention and time (T0/T1/T2/before and after each session) will be the fixed effects. The Akaike information criterion and binary logistic regression will be performed to explore significant influence factors.

Spearman rank correlation coefficient will be used to investigate the relationship between the self-reported measures and heart rate.

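### Therapist is balanced 50/50 within each arm but left out of the stated model; if the therapists differ, the tests become slightly conservative, and adding the factor costs almost nothing

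*Protocol article*

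**What the plan says.** Under Eligibility, Recruitment of Study Participants, and Randomization, the Protocol article makes therapist a balanced design factor. Two experimenters deliver the sessions, "each administering to 50% of the sample of each group to control for possible biases related to the" therapist's personality and competence. Both received the same training and were supervised. Participants are allocated to arms "based on a simple blinded randomization via an Excel (Microsoft Inc) file"; how the therapist split is reached is not described.

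Under Statistical Procedure and Data Analysis the comparison is a mixed-design repeated-measures ANOVA in which "individuals will be the random effect, while the type of intervention and time (T0/T1/T2/before and after each session) will be the fixed effects". Therapist is not among the terms. The only other wording on further factors is exploratory: "The Akaike information criterion and binary logistic regression will be performed to explore significant influence factors".

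Under The Integrated PMRT and Virtual Environment Design, Intervention B has no therapist in the first four sessions: "all sessions were self-managed within the Moodle platform".

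**The concern.** When a factor is forced into balance across arms, its contribution cancels from the arm difference. The true sampling variability of that difference therefore excludes it. A model without the factor still counts its variation as between-person error, so the reported standard error exceeds the true one. Intervals are then too wide, the test rejects too rarely under the null, and some power is lost.

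The trial has little power to spare. Under the plan's own inputs, 108 participants give power of about 0.81 against a target of 0.80, so even a small avoidable loss can take it below target.

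**Working it through.** **Inputs from the Protocol article (Power Calculation).** "The effect size was set as 0.25, the α as .05, and the Power" as 0.80; the test is described as "the repeated-measures ANOVAs between factors have been considered"; 3 groups, 3 measurements, 36 per group (N = 108). With the stated split, each therapist treats 18 of the 36 in each arm.

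**Assumptions (not in the documents).** The correlation between measurements is ρ = 0.5. The therapist difference is d, in SD of one measurement within therapist, shown at 0.2, 0.5 and 0.8. It is absent at T0, which precedes every relaxation session, and present at T1 and T2.

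**Step 1: the plan's own figure.** For the between-factors test, λ = f² × N × m / (1 + (m − 1)ρ) = 0.0625 × 108 × 3 / 2 = 10.125, with 2 and 105 degrees of freedom and critical F 3.083. Power is 0.809, and 108 is the smallest N divisible by three that reaches 0.80 (105 gives 0.797). So 36 per group reproduces with ρ = 0.5. With ρ = 0.3 the requirement would be 87, and with ρ = 0.7 it would be 129.

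**Step 2: variance left in the error term.** With SD 1, a person's mean over three measurements has variance (1 + 2 × 0.5)/3 = 0.667. The true SE of an arm difference is √(2/36 × 0.667) = 0.192. A difference d at two of three time points shifts the person mean by 2d/3. Split 50/50, it adds variance (2d/3)²/4 = d²/9. The relative inflation is r = (d²/9)/0.667, and the SE is multiplied by √(1 + r).

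**Step 3: power without the term.** The arm signal is unchanged and only the denominator grows, so power is approximately P(F′(2, 105; 10.125) > 3.083 × (1 + r)).

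| d | r | SE inflation | Power, therapist omitted | Power, therapist included |
|---|---|---|---|---|
| 0.2 | 0.0067 | 0.3% | 0.806 | 0.809 |
| 0.5 | 0.0417 | 2.1% | 0.79 | 0.809 |
| 0.8 | 0.1067 | 5.2% | 0.77 | 0.809 |

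The included column uses 104 error degrees of freedom; to three decimals the lost degree of freedom makes no difference. SE inflation depends only mildly on ρ. At d = 0.5 it is 2.6% for ρ = 0.3 (0.0278/0.533 = 0.052) and 1.7% for ρ = 0.7 (0.0278/0.8 = 0.035).

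**Step 4: the arm-by-time test.** This was simulated under the null with the same post-baseline pattern (20,000 trials per value, nominal 0.05).

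| d | Type I error, no therapist terms | With therapist-by-time |
|---|---|---|
| 0.2 | 0.048 | 0.049 |
| 0.5 | 0.040 | 0.048 |
| 0.8 | 0.037 | 0.055 |

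For the T0-to-T1 change, the true SE of an arm difference is √(2/36 × 1) = 0.236. Omitting therapist makes it √(2/36 × (1 + d²/4)) = 0.237, 0.243 and 0.254. A therapist main effect alone does not remove this, because it enters the between-person part of the model only. The therapist-by-time term is what removes it.

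**The case against.** The strongest reply is that the stated purpose was bias control and that the 50% split achieves it by design. That stands. A reader might infer that the purpose is lost in the analysis, or that the results risk false positives. The documents support neither: an additive therapist difference cancels from the arm contrast, and any error is conservative.

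Second, the model sentence may not be a closed list. The Results section reports that age and years of education were controlled for, although the sentence names neither, and this is a condensed article. This stands in part. Neither that passage nor the exploratory sentence names therapist, and the one factor the design deliberately balances is missing from a sentence that does list the effects.

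Third, the size rests on an assumption. Common training, supervision and standardized instructions make a large gap less likely, and at 0.2 SD the loss is negligible. This stands.

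A reader might also expect a larger loss by letting the therapist difference act at all three time points. In simulation, power is then 0.767 at 0.5 SD and 0.717 at 0.8 SD. That places an effect at T0, before any session, and a constant effect of this kind cancels from the arm-by-time test (simulated type I error 0.049 to 0.052).

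Finally, since the randomization is simple, a reader might infer that an uneven split lets the therapist difference leak into the arm comparison. The article states 50% of each group, and nothing shows a departure from it. If therapists had merely been assigned at random, omitting the term would leave type I error near nominal (simulated 0.049 to 0.052). The conservatism described here therefore depends on the stated split.

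**Conclusion.** The point holds as a modest, conservative inefficiency. A factor balanced within arms is absent from the stated model, so any difference between the therapists inflates the standard errors instead of being removed. With a difference arising after baseline and ρ = 0.5, the arm test loses about 0.3, 1.5 and 4 percentage points of power at 0.2, 0.5 and 0.8 SD. From about 0.5 SD this takes it just under the 0.80 target. The arm-by-time test is also conservative. The arm estimate is not biased and the false-positive rate is not raised.

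The conclusion rests on the exact 50/50 split and on a therapist effect that the documents do not give. If the therapists hardly differ, the omission is harmless.

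**What to change.** In Statistical Procedure and Data Analysis, add therapist (two levels, fixed) and therapist-by-time to every between-arm repeated-measures model. With only two therapists, a fixed effect is more suitable than a random one. Report arm-by-therapist estimates descriptively: Intervention B has no therapist in t1 to t4, so a single common therapist effect may not fit all arms.

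With three measurements the cost is one between-person degree of freedom (105 to 104) and two within-person (210 to 208). The sample size stays at 108. No new data are needed, provided the trial records show which therapist treated each participant, as a deliberate 50% split implies.
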